**Table utbl0001:** 

Subject area:	Neuroscience
More specific subject area:	Effects of bilateral cathodal tDCS application in muscle strength and pulmonary performance in the young and elderly population.
Name of your protocol:	Bilateral transcranial direct-current stimulation on muscle strength and respiratory endurance: randomized, placebo-controlled, double-blind trial protocol
Reagents/tools:	Bilateral tDCS: Neuromodulator from Microestim Foco Research, NKL, Santa Catarina, Brazil. Forced vital capacity (FVC), Forced Expiratory Volume in 1 S (FEV1), FEV1/FVC Ratio, Maximal Voluntary Ventilation (MVV): SPM-A spirometer CONTEC™, China Powerbreathe K5 equipment (Powerbreathe, Southam, England): S-INDEX, Flow and Volume. Handgrip strength: hydraulic dynamometer (Saehan, Beijing, China).
Experimental design:	Randomized placebo-controlled double-blind trial. Four groups (*n* = 68), test (young and elderly, *n* = 34) and placebo (young and elderly, *n* = 34). Outcome measures were evaluation of lung function, strength of inspiratory muscles, general strength. After a basal evaluation, the outcomes were tested in two separated moments before and after bilateral cathodal tDCS stimulation both comparing in the same age group and comparing elderly versus young.
Trial registration:	U1111–1310–2605, International Clinical Trial Registry Platform
Ethics:	The study was conducted in line with recommendations from the Declaration of Helsinki and received ethical approval from the Ethics Committee of the Federal University of the Amazonas, Brazil [CAAE66350622.0.0000.520, evaluation 315.763].
Value of the Protocol:	tDCS is proven to be a valuable tool in rehabilitation and performance enhancement in several areas, but with little or no work done in respiratory function or respiratory rehabilitation. The main objective is to evaluate the expected improvement of the respiratory muscle strength and resistance after intervention with bilateral tDCS over the primary motor cortex in healthy young and elderly subjects. It is a randomized, double-blinded study designed to study the possibility of using tDCS for enhance respiratory performance in healthy subjects or in rehabilitation programs after respiratory injury. We highlight the construction of the study, allowing the comparison between the response in the young and the elderly.

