### Research questions

-Compared to controls, is cathodic bilateral tDCS stimulation effective in improving muscle strength and respiratory performance?-Will there be a change in the effects of cathodic bilateral tDCS when performed in the young vs. elderly regarding muscle strength gain/better respiratory performance?

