### Sample size and subject recruitment

The volunteers were recruited after posting invitation posters on the campus of the Federal University of Amazonas. No compensation was offered for participation in the experiment. All the subjects were female. The rationale for this was the ease of recruiting female participants, since there are activities taking place on the university campus only for elderly female.

Were inclusion criteria for the young group – ages comprehended between 18 and 25, no medical history of cardiovascular, pulmonary or neurologic conditions affecting the respiratory tract. Regarding the elderly group the inclusion criteria were the same, except the timeframe, considering ages between 60 and 80 years of age. Exclusion criteria were subjects out of the timeframe requested by the study protocol in both groups, medical history of cardiovascular, pulmonary or neurologic conditions. Also, in the selection of volunteers for the young group, those who were at the time of their menstrual period were excluded to avoid any hormonal influence on the results.

For the sample size, inspiratory muscle strength will be used through the dynamic inspiratory pressure (*S index*). As there is no study that evaluated this type of variable associated with tDCS, we will accept a priori a Cohen's size effect *F* = 0.25 (Small Effects). For sample size, ANOVA two-way repeated measures (Between-within) was calculated. Parameters used were size effect 0.25, α = 0.05, β = 80 %, 2 groups, 2 measurements (tDCS stimuli and Sham stimuli), correction between measurements = 0.5 and correction of no-sphericity ε = 1. Accepting a possible 20 % of sample loss, a sample calculation of 40 volunteers was selected both for the elderly and young group, with a global total of 80 subjects and G power 3.1 (University of Dusseldorf, Dusseldorf, Germany) was used for calculation.

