The stratification randomization (age, BMI, FVE1 and FVC) was electronically conducted by an investigator that did not take part in the evaluation of patients of application of the tests. Electronic codes were generated to introduce in the tDCS neuromodulator ensuring the blinding of the therapist and the subject assessed (doble blind). The volunteers of this research will be randomized in four groups: 20 volunteers per group, being 20 for young interventional and young placebo, and the same for the elderly. After a basal (day 1) evaluation all subjects will be part of two evaluation/intervention rounds with 48 to 72 h interval (Fig. 1).

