### Statistical analysis

The data will be expressed as mean and standard deviation of the mean, median and interquartiles, and percentage. Initially, normality will be tested using the Shapiro Wilk test and homogeneity using Levene's test. For mean analysis, the unpaired *t*-test or Mann-Whitney test will be used. For the evaluation of the intervention, ANOVA two-way (between-within) *post hoc* Bonferroni test will be used. If normal values are not present, the Kruskal-Walli's test will be performed for unpaired values and the Friedman test for paired data, with Bonferroni correction for the *p*-value. Effect size calculation will be done using the G*Power 3.1 software, and statistical analysis will be conducted using the JAMOVI software (Jamovi project, Australia) and GraphPad Prism 8.0 (GraphPad, USA). Significant values accepted as *p* < 0.05

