## Protocol validation

Data analysis for the protocol is currently ongoing. An example of a JAMOVI data file for the analysis can be found in the Supplemental section. Data analysis includes ANOVA two-way (between-within) models.

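### The two-way between-within ANOVA contains no age-by-arm-by-time contrast, so it cannot test the second research question, whether the cathodal tDCS effect differs between young and elderly

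*Protocol article*

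**What the plan says.** The Research questions section of the protocol article poses two questions. The second is "Will there be a change in the effects of cathodic bilateral tDCS when performed in the young vs. elderly". The specifications table describes the outcome comparisons as "both comparing in the same age group and comparing elderly versus young", and the same table presents the young-versus-elderly comparison as a particular strength of the design.

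Allocation is by age and arm: "The volunteers of this research will be randomized in four groups: 20 volunteers per group", that is, active and sham within each age band. Each participant is tested before and after stimulation in the same session.

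The same model appears in three places:
- Sample size and subject recruitment: "For sample size, ANOVA two-way repeated measures (Between-within) was calculated", with two groups and two measurements.
- Statistical analysis: "For the evaluation of the intervention, ANOVA two-way (between-within) *post hoc* Bonferroni test will be used".
- Protocol validation: "Data analysis includes ANOVA two-way (between-within) models".

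The article does not name the levels of the between factor, and it mentions no three-factor model, arm-by-age interaction or difference-in-differences contrast.

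**The concern.** A two-way between-within ANOVA has one between-subject factor and one within-subject factor. Within a session the design has two between-subject factors (age band and arm) and one within-subject factor (pre/post). Whether age changes the stimulation effect is the question of whether the active-minus-sham difference in pre-post change differs between young and elderly. No term of the stated model corresponds to that.

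An analyst who follows the text will therefore probably answer the age question informally, by noting that one age group reached significance and the other did not. That pattern is common by chance when both ages respond equally. The article says that data analysis is under way, so the wording needs correcting before results by age are written up.

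**Working it through.** **Inputs from the article.** Effect size f = 0.25, α = 0.05, power 80%, 2 groups, 2 measurements, correlation 0.5, ε = 1, 20% loss, 40 per age group and 80 in total (Sample size and subject recruitment); 34 active and 34 sham, 68 in total (specifications table); 20 per cell (randomization paragraph). SD below means the SD of the pre-post change.

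**Step 1: reproduce the stated sample size.** For the within-between interaction, λ = f²·N·m/(1−ρ), with df (k−1)(m−1) and (N−k)(m−1). With k = 2, m = 2 and N = 34, λ = 0.0625 × 34 × 2 / 0.5 = 8.5 and power is 0.807, so N = 34. Two age groups give 2 × 34 = 68, matching the table. With loss, 34 × 1.2 = 40.8, against 40 printed. Four groups in one model would have needed only 48 in total. The sizing therefore fits one active-versus-sham × time ANOVA per age group.

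In a two-group comparison of change, λ = N·d²/4. Setting 34·d²/4 = 8.5 gives d = 1.0, so the planned effect is 1.0 SD of change.

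**Step 2: look for the age contrast under each workable coding.**
- One ANOVA per age group (active/sham × time): tests arm within that age; no age term.
- Ages pooled (active/sham × time): tests arm overall; no age term.
- Four cells as one between factor × time: a 3-df omnibus test that does not isolate the age-by-arm contrast. Pairwise post hoc comparisons of group means are not differences of differences.

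**Step 3: the per-age coding and p-value comparison.** If both ages have the same true effect and each test has power p, exactly one is significant with probability 2p(1−p).
- 1.0 SD, 17 per arm: p = 0.807; 2 × 0.807 × 0.193 = 0.31.
- 1.0 SD, 20 per arm: p = 0.869; 2 × 0.869 × 0.131 = 0.23.
- 0.5 SD, 20 per arm: p = 0.338; 2 × 0.338 × 0.662 = 0.45.

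**Step 4: the four-cell coding.** Suppose there is no tDCS effect but the ages differ by δ in practice or fatigue. The documents give no value for δ, so a range is assumed. Cell mean changes are (0, 0, δ, δ), so λ = 4n(δ/2)² = nδ², with 3 and 4n−4 df.

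| δ (SD of change, assumed) | λ at n = 20 | Rejection rate, n = 20 |
|---|---|---|
| 0 | 0 | 0.05 |
| 0.25 | 1.25 | 0.13 |
| 0.5 | 5 | 0.42 |
| 1.0 | 20 | 0.97 |

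An equal tDCS effect of 1.0 SD in both ages also gives λ = 20 and 0.97, so this test cannot tell the two situations apart. In simulation (40,000 replicates, 20 per cell, δ from 0 to 1.0 SD), the per-age tests stay at about 0.05 and the pooled test falls from 0.05 to 0.03. Neither is inflated.

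**Step 5: power of the contrast that answers the question.** For a between-age difference of 1.0 SD in effect:
- Three-way ANOVA: SE = √(4/n), 4n−4 df. Noncentrality is 1/√(4/17) = 2.06 and 1/√(4/20) = 2.24; power is 53% (17 per cell) and 60% (20 per cell).
- Post value adjusted for pre value: at correlation 0.5 the residual variance is (1−0.25)σ² = 0.75σ², while the variance of change is 2(1−0.5)σ² = σ². So SE = √(3/n), with 4n−5 df. Noncentrality is 2.38 and 2.58; power is about 65% and 72%.

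**The case against.** The strongest reply is that the main comparison is sound. The primary outcome is test versus sham, and a two-way ANOVA run within each age group tests that validly. Age modification is the second question in a study presented as a step towards larger ones. This stands, and it limits the point to the second question.

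A reader might infer more: that the plan will turn an age difference in practice or fatigue into a spurious intervention effect. The documents do not support that as a general statement. It happens only if the four cells are coded as one between factor. The article does not state that coding, and its sample size points to one ANOVA per age group, where there is no inflation. The size of any practice difference is also an assumption. Nor does the plan say that all pairs of cells will be compared; it names only a Bonferroni post hoc test.

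Two further defences fail. Read literally, the sample-size paragraph has tDCS and sham as the two repeated measurements. With age as the between factor, the two-way interaction would then be the age test. But each participant belongs to one arm only, so that design was not run. It might also be said that a fuller analysis plan could add the missing term, since the Protocol validation section says only that the analysis includes such models. Yet the article fixes the same model in three places and names no parametric alternative for the intervention effect, so the objection is to what is stated.

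**Conclusion.** The concern holds for the second research question. Under every workable coding, the two-way model lacks the age × arm × time contrast. On the coding that fits the sample size, active versus sham within each age is tested properly, but any statement about age would rest on comparing p-values. If both ages truly share the planned effect of 1.0 SD of change, that comparison suggests a difference in 23% of trials (20 per arm) to 31% (17 per arm). Inflation from age differences in practice (about 13%, 42% and 97% rejection at 0.25, 0.5 and 1.0 SD, with 20 per cell) is conditional on a four-cell coding that the article does not state and on values that it does not give.

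The right contrast is itself imprecise: the trial was sized for arm × time within one age group, not for a difference between ages. The power figures assume the protocol's correlation of 0.5, equal variances across cells and α = "Significant values accepted as *p* < 0.05".

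**What to change.** State the following in the Statistical analysis section.

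- Analyse the cathodal session (day 2) for the two research questions, which concern cathodal stimulation. Analyse the day 3 session, where electrode polarity is reversed, separately.
- Fit one model to all participants with arm, age group and arm × age on the post value adjusted for the pre value (preferred). A three-way age × arm × time ANOVA is an acceptable alternative. It targets the same contrast but is not equivalent and has lower power at the protocol's correlation.
- Report active minus sham within each age group for the first question. Report the 1-df age-by-arm contrast with its 95% CI as the only test of the second.
- State that no age difference will be inferred from differing p-values in the two age groups.
- Label the interaction exploratory and give its power for a 1.0 SD-of-change difference between ages: about 65% to 72% with baseline adjustment, or 53% to 60% with the three-way ANOVA (17 to 20 per cell).

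The cost is a change of analysis wording, with no new data. The downside is that the age comparison is openly reported as low-powered.

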### Primary outcome measurements

Primary outcome is the increase in strength and lung function in the test groups compared to the sham group.

Lung function was performed with spirometry evaluation. Forced vital capacity (FVC), Forced Expiratory Volume in 1 S (FEV1), FEV1/FVC Ratio, Maximal Voluntary Ventilation (MVV) were the spirometry parameters evaluated using the SPM-A spirometer (CONTEC, China).

Inspiratory muscle endurance will be measured with Powerbreathe K5 equipment (Powerbreathe, Southam, England), using the S-INDEX, Flow and Volume. The handgrip strength will be checked using a hydraulic dynamometer (Saehan, Beijing, China).

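### The non-parametric fallback names no counterpart to the group-by-time test, so it does not state how the increase on active versus sham would be tested if normality fails

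*Protocol article*

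**What the plan says.** Under Primary outcome measurements, the protocol article states: "Primary outcome is the increase in strength and lung function in the test groups compared to the sham group". That is a difference between arms in change.

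The Statistical analysis section gives the main method as "For the evaluation of the intervention, ANOVA two-way (between-within" factors, with Bonferroni post hoc tests. It opens with assumption checks: "Initially, normality will be tested using the Shapiro Wilk test and homogeneity using Levene's test". If values are not normal, Kruskal-Wallis "test will be performed for unpaired values and the Friedman test for paired data", with Bonferroni correction. The section does not say which variable enters either test (pre, post or change), which groups or occasions are compared, or how many comparisons the correction covers. For what it calls mean analysis it also lists an unpaired t-test, and adds "test or Mann-Whitney test will be used", again without naming the variable.

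The Step-by-step study design has each subject tested before and after stimulation on Day 2 and again on Day 3. The Protocol validation section says that data analysis is under way.

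**The concern.** The main analysis answers the trial's question with one test, the group-by-time interaction. The fallback replaces it with two tests sorted by whether the data are paired. The natural reading is that Friedman looks at change within subjects and Kruskal-Wallis looks at levels between groups. The quantity of interest, change in one arm minus change in the other, falls between them.

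What is at stake is the claim an analyst could make while following the text. All outcomes are maximal-effort manoeuvres repeated after a 30-minute session, so a shift common to both arms (learning or fatigue) is plausible. A significant Friedman test in the active arm alone would not separate such a shift from an effect of stimulation.

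The branch may well be used. Eight measures are named (FVC, FEV1, their ratio, MVV, S-index, flow, volume, handgrip). Suppose Shapiro-Wilk is applied at 5% to each of the four arm-by-time cells of an outcome. Treating the cells as independent, exactly normal data would still trigger the switch with probability 1 − 0.95⁴ = 18.5% per outcome and age group. Some outcomes could then be analysed by a test of the trial's question and others by tests of a different one.

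**Working it through.** **1. The plan's own figure.** Inputs from Sample size and subject recruitment: "Parameters used were size effect 0.25", α = 0.05, power 80%, two groups, "2 measurements (tDCS stimuli and Sham stimuli"), and "correction between measurements = 0.5".

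- Noncentrality for the within-between interaction: λ = f²·N·m/(1 − ρ). With N = 34 this is 0.0625 × 34 × 2 / 0.5 = 8.5.
- The critical F(1, 32) is 4.149, and power is 0.807. N = 32 gives 0.781.
- So 34 per age group is needed, which matches the 68 in the specifications table (17 per arm in each age group). A between-group test would need 98.
- The pure within-subject test gives the same 34, so the match does not separate it from the interaction. It does show that the trial was sized on change, not on levels.
- In a 2 × 2 layout, f = 0.25 means cell effects of ±0.25 SD, so a difference in change of 4 × 0.25 = 1.0 SD.

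**2. What Friedman tests.** With two occasions it is a sign test. If k of n subjects improve, the statistic is (2k − n)²/n on 1 df. Arm does not appear. With four occasions (pre and post on two days) it compares more occasions, still without arm.

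**3. Its rejection rate with no tDCS effect.** Assumptions not in the documents: normal data and a common shift s in both arms. The SD of change is √[2(1 − 0.5)] = 1, so a subject improves with probability Φ(s).

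For n = 17, the test rejects at 0.05 when k ≥ 13 or k ≤ 4. At 0.025 (Bonferroni over two arms) it rejects when k ≥ 14 or k ≤ 3. Exact binomial results, where P is the active-arm rejection rate and P(1 − P) is the chance that active is significant and sham is not:

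| Shift | Φ(s) | P at 0.05 | P(1 − P) | P at 0.025 | P(1 − P) |
|---|---|---|---|---|---|
| 0 | 0.500 | 4.9% | 4.7% | 1.3% | 1.3% |
| 0.3 SD | 0.618 | 16.1% | 13.5% | 6.3% | 5.9% |
| 0.5 SD | 0.691 | 36.0% | 23.0% | 18.1% | 14.9% |

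Simulation gave 16% and 36% uncorrected, and 6.5% and 19% corrected, in agreement. With the planned 20 per arm, the uncorrected rate at 0.5 SD is 38% (39% by simulation). Simulated skewed data, the case in which the fallback applies, gave 77%.

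**4. What Kruskal-Wallis tests.** For active versus sham on post values, with 20 per arm, simulated type I error is 4.4–5.1% with or without the shift. It is a valid between-arm comparison. Its power relative to change scores depends on ρ:

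- At ρ = 0.5 the variance of change, 2(1 − ρ), equals 1, the same as that of the post value. Nothing is lost: simulated power is 0.784 (post) against 0.780 (change) at 17 per arm and a 1 SD effect.
- At an assumed ρ = 0.8 the SD of change is √0.4 = 0.632. An assumed 0.6 SD effect becomes 0.6/0.632 = 0.95 SD on the change scale. Simulated power is about 38% (post) against about 75% (change).

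**5. The proposed replacement.** Two-group Kruskal-Wallis on pre-to-post change is the Mann-Whitney test on change; the p-values agree. With 20 per arm and ρ = 0.5, its type I error is 4.4–5.0% with or without the shift. Its power at f = 0.25 is 0.86–0.87 (normal) and 0.97 (skewed). The ANOVA interaction gives 0.87–0.88 and 0.83–0.84.

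**The case against.** A reader might infer that the fallback cannot test active against sham at all, and that the trial loses its controlled comparison. The documents do not support that. Kruskal-Wallis between randomised arms on post values is a controlled comparison and keeps its level. On change scores it is the very test proposed here, and the text neither specifies nor excludes change scores. This stands.

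The power loss is absent at the only correlation that the documents give. This also stands: the 38% against 75% contrast needs an assumed correlation of 0.8 and an assumed effect of 0.6 SD.

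The Friedman figures rest on an assumed practice shift, and the design limits practice effects through warm-up inhalations and best-of-several scoring. Bonferroni roughly halves the rate at 0.5 SD. Nothing says that efficacy will be judged arm by arm. All of this is fair, and the rates above are conditional on it. The Day 1 session, however, describes only forced-expiration spirometry, so it offers no familiarisation with MVV, dynamic inspiratory strength or handgrip.

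A reader might also infer that normality will be tested on raw values and not residuals. The article does not say what Shapiro-Wilk is applied to, and its wording is too loose to carry that charge.

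Finally, a fuller analysis plan might supply the contrast. It might, but the article does more than stay silent: it names the two fallback tests, and neither is stated as a test of the difference in change.

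**Conclusion.** The point holds in a limited form. The main analysis is suited to the primary question. The weakness is confined to the branch taken when normality fails, where one interaction test is replaced by two tests with no stated counterpart to it. Friedman makes no active-sham contrast on any reading. Kruskal-Wallis makes one, but on an unstated variable.

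The false-positive risk arises only if within-arm Friedman results are read as efficacy and both arms share a shift. It is nil beyond the nominal 5% with no shift, and reaches 36% (18% after correction over two arms) at 0.5 SD with 17 per arm, normal data and correlation 0.5. Any loss of power from analysing post values arises only if the pre-post correlation exceeds the protocol's 0.5.

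**What to change.** In Statistical analysis, state that the non-parametric fallback for evaluating the intervention is a Mann-Whitney test (equivalently, two-group Kruskal-Wallis) of pre-to-post change in the session concerned, active versus sham, within each age group. Report it with a Hodges-Lehmann difference and 95% confidence interval. State that Friedman results are descriptive, within arm, and not evidence of efficacy. State that normality is checked on the model residuals; with two time points, for the group-by-time term, these are the deviations of change from the arm mean.

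The cost is small. Mann-Whitney is already in the plan and no data need to be collected. Because analysis is already under way, the change should be dated, with a note of whether results by arm had been seen.
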